**B. Rationale for Design and Control**

Our design can significantly strengthen the conclusions of Wolters et al. (1996) in three ways. First, with the parallel group, placebo-controlled design, we can show whether olanzapine is superior to placebo in treating PD psychosis. Second, with a fixed dose design we can address the question of optimal olanzapine dose in these patients. Third, the Wolters et al study did not use blinded ratings of psychosis. To address this, we will videotape clinical interviews at each study visit. The main outcome measure, BPRS ratings of psychosis, can then be rated after the end of the study by an investigator who will be blind not only to olanzapine dose but also to duration of treatment (0, 2, or 4 weeks). This will allow us to show that improvement in any treatment group is not due to investigator or patient expectation of improvement, and may also increase our power as the placebo group may show less change.

We chose 4 weeks rather than a longer study period because clinical experience and the Wolters et al. trial both suggest that improvement in psychosis is usually seen by this point.

The doses chosen are due in part to the desire to bracket the mean final dose in the open study (7mg/day), and in part to the fact that olanzapine is marketed in 5mg and 10mg tablets.

A placebo control is not only scientifically needed but also ethically justified, given the potential side effects of either olanzapine or other treatments of psychosis in this population (beyond the conservative measures we require for study entry).

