#### **2. Sample Size and Statistical Justification**

Sample size will be 10 patients per arm (30 total). Using the Wolters et al baseline data as a rough estimate of variance, a power analysis shows that we would have a 90% likelihood of detecting a 50% improvement in total BPRS scores (at  $\alpha = 0.05$ ) within a single treatment group of 10-11 patients. From the same data, power would be slightly higher using the BPRS "positive item" subscale (*i.e.*, the 4 items which reflect hallucinations, delusions, or formal thought disorder).

To rigorously estimate power for our study design would require an estimate of the variance in the *change* of BPRS scores with olanzapine (or placebo). We do not have that data. However, we suspect on clinical grounds that there will be no meaningful improvement in the placebo group (here is where the blinded videotape ratings may add to our power), so we expect to also find a significant difference between groups, using a comparable number of patients per treatment arm. Efficacy will be compared across all 3 groups.

Due to some uncertainty about the power of the study as described above, we have the following backup plan. After enrolling 30 patients, we plan to submit the primary outcome data, together with the sealed code for unblinding the data, to a statistical consultant who will not otherwise participate in the study. If statistically significant differences in efficacy are apparent among the 3 arms at this point (*i.e.*,  $p < 0.01$ , ANOVA), we will conclude enrollment and further analyze the results. Otherwise we will seek to enroll an additional 5 subjects in each arm before we are informed of the study code.

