##### **1. Materials and Supplies**

We will use matching dose cards, one for each week of the study, each with 9 days’ supply of drug. The last 2 days will be clearly marked as extras, and will be used to better assess compliance and in the event that a patient is a day or two late returning to clinic. Each card will be marked “Week 1”, “Week 2”, etc., as appropriate. Each card will also be marked with a code (e.g. A, B, or C) which will indicate which study arm is involved. Here, “A”, “B”, and “C” refer to the placebo, 5mg, and 10mg arms, but of course not necessarily in that order. We will also ask Lilly to supply us simultaneously with a sealed envelope containing the code, *e.g.* A=placebo, etc. This envelope will remain sealed until 30 patients have been enrolled, as described above.

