## **IV. Data Analysis Methods (including any interim analyses)**

The 0-2 week and 2-4 week periods will be treated as two separate study periods for the purpose of statistical analysis, due to the possible addition of dopamimetics at the 2-week visit; the change from 0 to 2 weeks will be the primary test of efficacy. If we have few dropouts, a repeated-measures ANOVA with post-hoc tests would be adequate and powerful (dependent variable: BPRS positive symptom subscale scores; grouping variable: dose; within variable: time). Otherwise a more complicated actuarial analysis might be needed. We have collaborated in the past with the biostatistics group here at Washington University. Investigators will remain blinded throughout accrual and treatment. See section III.D.2. above for a preliminary analysis of data, after treatment of 30 subjects, by a statistical consultant not otherwise participating in the study.

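### The look at 30 patients has no matching final significance level (about 5.4% overall error if the final test is at 0.05), and it cannot run as timed

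*Protocol*

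**What the plan says.** **The two tests.** Protocol III.D.2 sets 10 patients per arm. Once 30 are enrolled, the primary outcome data and the sealed code go to a consultant with no other part in the study. The stopping condition begins "If statistically significant differences in efficacy are apparent among the 3 arms at this point" and is specified as an ANOVA p-value below 0.01. If it is met, enrolment closes. If it is not: "Otherwise we will seek to enroll an additional 5 subjects in each arm before we are informed of the study code". That takes the trial to 15 per arm, 45 in all. Section IV makes the 0 to 2 week change the primary test of efficacy. No level is given for the analysis at 45. The only other level in the document is the 0.05 in III.D.2, attached to a claim of "90% likelihood of detecting a 50% improvement in total BPRS scores" "within a single treatment group of 10-11 patients".

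**The timing of the look.** III.B says that the BPRS ratings, described there as the main outcome, "can then be rated after the end of the study", by a rater blind to dose and to time on treatment. III.F.1 says of the code: "This envelope will remain sealed until 30 patients have been enrolled". Section IV, referring back to the same look, places it "after treatment of 30 subjects".

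**The concern.** The protocol fixes one half of a two-look rule and leaves out the other. A trial that can succeed at 30 and, failing that, at 45 has two chances of a false positive. If the second test takes the full 0.05, the total must exceed 0.05.

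The look is also not executable as described. It needs BPRS ratings, and the rating step is placed after the point that the look is meant to decide. Under the enrolment trigger, the data would be incomplete for the most recent patients. A stopping decision on partial primary data, or a hurried change to the rating procedure, would weaken the blinded rating that III.B presents as a main advantage over the cited open study.

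**Working it through.** **1. The plan's own figure.** The protocol gives no overall type I error, so there is none to reproduce. The one figure tied to 0.05 is the 90% power within a single group. It cannot be checked, because the baseline mean and SD come from the cited open study and are not in the protocol. Solved backwards with the noncentral t (two-sided 0.05), 90% power implies:
- paired test, df = n−1, noncentrality d√n: d = 1.15 for n = 10, 1.09 for n = 11;
- baseline variance treated as for two independent samples, df = 2n−2, noncentrality d√(n/2): d = 1.53 for n = 10, 1.45 for n = 11.

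This concerns change within one arm. It does not set a level for the three-arm test at 45.

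**2. Overall error of the two-look rule.**

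Inputs from III.D.2: three arms; 10 per arm at the first look; stop if p<0.01; otherwise 15 per arm in total. Assumption: final level 0.05, the only other level named.

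Test at each look, on the change score, with n per arm, arm means m_j and grand mean m:

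F = [n Σ(m_j − m)² / 2] / [ΣΣ(x_ij − m_j)² / (3n − 3)]

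The degrees of freedom are (2, 27) at n = 10 and (2, 42) at n = 15. With two time points, the dose-by-time test of the repeated-measures ANOVA in section IV is this same F on the change.

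Overall error = P(p₃₀<0.01) + P(p₃₀≥0.01 and p₄₅<0.05).

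Simulation of 4,000,000 null trials, normal data, equal arms:

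| Quantity | Result |
|---|---|
| P(p₃₀<0.01) | 0.0099865 |
| P(p₃₀≥0.01 and p₄₅<0.05), by subtraction | 0.0437580 |
| Overall | 0.0537445 (simulation SE 0.0001) |
| Upper bound, 0.01 + 0.05 | 0.06 |
| If both looks used 0.05 | 0.0790 |
| Overall with final level 0.04 | 0.0442 |
| Final level that gives 0.05 overall | 0.0461 |

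The excess over 5% is 0.0537 − 0.05 = 0.0037, under 0.4 percentage points. It is small because the first look is strict. A separate run of 1,000,000 trials with a final level of 0.046 gave 0.0498.

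**3. Can the look take place as timed?**

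| Place | What it fixes |
|---|---|
| III.B | tapes rated after the study ends |
| III.D.2 | look on primary outcome data after 30 enrolled |
| III.F.1 | code sealed until 30 enrolled |
| IV | look after 30 treated; primary outcome is the 0-2 week change |

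- *Rating.* If the look says continue, ratings of the first 30 must already exist while 15 more patients are still to enrol, so they cannot have waited for the end. If it says stop, the rating fits III.B only in hindsight, since the ratings were needed to reach that decision.
- *Trigger.* Treatment lasts 4 weeks. On the day the 30th patient enrols, everyone enrolled in the preceding 2 weeks lacks the 2-week visit, and everyone enrolled in the preceding 4 weeks is still on study drug. The enrolment and treatment triggers can therefore differ by 4 weeks, and under the first the primary outcome is incomplete.

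**The case against.** **The final level is not stated.** A reader might infer that the protocol sets 0.05 at 45 patients and so definitely exceeds 5%. It does not say so. The 0.05 belongs to a within-group power statement, and a separate analysis plan, not seen here, could set a lower level. This stands: the 5.4% is conditional. But the protocol itself fixes the interim threshold and stopping rule, and section IV is the place it assigns to interim analyses, so the matching final level belongs there too.

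**The excess is small.** Also true. On its own it would be a minor point in a trial of 30 to 45 patients, but a single sentence removes it.

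**The wording can be read consistently.** III.D.2 sends data together with the code, so the data must exist by then. Section IV can be taken as the operational meaning. III.B says only that tapes *can* be rated at the end, and 30 is the planned size with 45 a contingency. This reading is reasonable and shows that wording is enough to repair the problem. It does not remove it, because two sections name enrolment as the trigger and no section provides for rating before the look.

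**Unblinding.** A reader might infer that the sections disagree on who sees the code. They do not. III.D.2 gives it to the outside consultant, and both III.D.2 and section IV keep the investigators blind. The difference is only in when.

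**Use of CGI.** A reader might also infer that, without rated tapes, the stop decision would fall to the CGI, the other listed primary measure. Nothing says so; section IV names the BPRS positive-symptom subscale as the dependent variable.

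**Conclusion.** The point holds in a limited form and should be corrected. The plan tests the three arms twice and makes no allowance for the first test. If the final omnibus test is at 0.05, overall type I error is about 5.4% rather than 5%. This assumes normal data, equal arms with no dropouts, one endpoint, the same overall F test at both looks, and a crossing at 30 counted as a positive result. It does not cover pairwise dose comparisons or the CGI as a second primary measure.

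The timing fault does not depend on the assumed 0.05. As written, the look needs ratings that III.B places after the study, and its trigger differs between sections. Followed literally, III.D.2 gives a look without complete primary data. The documents do not support a claim that the stated alpha is certainly breached, or that the investigators would be unblinded.

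**What to change.** 1. In III.D.2 and section IV, state that if enrolment continues to 45, the final omnibus ANOVA is significant only at about p<0.046, keeping p<0.01 at the first look. If an analysis plan already sets a level that accounts for the first look, refer to it instead.
2. Use one trigger throughout: all 30 patients have at least their 2-week outcome (or have completed treatment, as section IV says), and their tapes have been rated in random order by the blinded rater. The 2-week outcome is enough for the primary test; waiting for week 4 is an option, not a necessity.
3. Amend III.B to provide for rating the first 30 patients' tapes before the look, and the remaining tapes later if enrolment continues.
4. Amend III.D.2 and III.F.1 to the same trigger, and say in III.F.1 that only the outside consultant opens the envelope.

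Cost: a final threshold of 0.046 instead of 0.05; a wait after the 30th enrolment of 2 weeks (4 if completion of treatment is chosen) plus rating time; and wording changes in four places. The planned sample sizes do not change.

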#### **E. Patient Assignment to Treatment**

The order of assignment to one of the three treatment arms will be random.

#### **F. Dosage and Administration**

See the summary table in III.A. for an overview. Patients who meet entry criteria will take identical study tablets nightly, containing either 5mg or 10mg olanzapine or placebo. Due to concerns about the tolerability of starting olanzapine abruptly at the 10mg qhs dose, we plan to administer only 5mg nightly for the first week of the “10mg” arm.

##### **1. Materials and Supplies**

We will use matching dose cards, one for each week of the study, each with 9 days’ supply of drug. The last 2 days will be clearly marked as extras, and will be used to better assess compliance and in the event that a patient is a day or two late returning to clinic. Each card will be marked “Week 1”, “Week 2”, etc., as appropriate. Each card will also be marked with a code (e.g. A, B, or C) which will indicate which study arm is involved. Here, “A”, “B”, and “C” refer to the placebo, 5mg, and 10mg arms, but of course not necessarily in that order. We will also ask Lilly to supply us simultaneously with a sealed envelope containing the code, *e.g.* A=placebo, etc. This envelope will remain sealed until 30 patients have been enrolled, as described above.

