#### **G. Blinding**

The study will be conducted in a double-blind fashion. See III.F.1., immediately above.

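### One visible letter per arm and a single key envelope mean that one code break would unblind every patient, and one correctly inferred letter would unblind its whole arm

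*Protocol*

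**What the plan says.** Protocol III.F.1 (Materials and Supplies) describes one card per week of treatment: "Each card will also be marked with a code (e.g. A, B, or C) which will indicate which study arm is involved". The key is a single document: "We will also ask Lilly to supply us simultaneously with a sealed envelope containing the code". On timing: "This envelope will remain sealed until 30 patients have been enrolled, as described above".

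III.G (Blinding) states "The study will be conducted in a double-blind fashion" and for all detail refers back to III.F.1. Section IV adds "Investigators will remain blinded throughout accrual and treatment". III.E says only "The order of assignment to one of the three treatment arms will be random". III.D.2 sets 10 patients per arm, with 5 more per arm if the look at 30 patients is not significant. The sealed code goes to an outside statistical consultant for that look.

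The protocol describes no patient-specific kit number, no code break for a single patient, and no new lettering for the extension. It adds one separate safeguard: under III.B, psychiatric interviews are videotaped and the BPRS is rated after the study by someone blind to dose and visit.

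**The concern.** A letter that stands for an arm links every patient in that arm. Anyone who sees the cards can add up sedation, motor change or benefit over all patients with the same letter, and each new patient adds evidence about the earlier and later ones. The single key has the same weakness in sharper form: it cannot be consulted about one patient without disclosing the rest.

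At stake are the assessments made at the visit. The CGI is listed as primary beside the BPRS (section I, Primary and Secondary Efficacy Measures) and is scored at follow-up by physician, patient and caretaker. UPDRS motor ratings are a primary safety measure, and nothing puts them on tape. The dopamimetic increase at week 2 is a judgement made in clinic, and it bears on the weeks 2-4 results and on objective 4. A rater or clinician who has decoded a letter could be swayed in any of these. The trial's stated rationale is to improve on an open study with unblinded raters, so the strength of the blind is central to it.

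**Working it through.** The protocol gives no figure on this point to reproduce. Its arm sizes are consistent: 3 × 10 = 30 and 3 × 15 = 45.

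**1. What one code break reveals.** There are three letters and one key. Opening the key decodes all three: 30 of 30 patients, or 45 of 45 after extension. With one envelope per patient, a break reveals 1 of 30 (3%).

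**2. What one inferred letter reveals.** Three letters can be matched to three arms in 3! = 6 ways. Knowing one letter exposes 10 of 30 patients (15 of 45) and leaves 2! = 2 keys. Knowing two letters exposes everyone. No re-lettering is stated, so knowledge gained in the first 30 would carry into the extension.

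**3. How much pooling helps.** The protocol gives no side-effect rates, so those below are assumptions. An observer takes the letter with the fewest affected patients as placebo, breaking ties at random (200,000 simulated trials per row; chance is 33%).

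| Assumed rates, placebo / 5 mg / 10 mg | Correct, 1 patient per letter | 5 per letter | 10 per letter |
|---|---|---|---|
| 10% / 20% / 30% | 39% | 56% | 67% |
| 10% / 30% / 50% | 47% | 74% | 86% |
| 20% / 40% / 60% | 48% | 71% | 82% |
| 10% / 50% / 70% | 60% | 91% | 98% |

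The rise from left to right is what the shared letter contributes.

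**4. Guessing the next letter.** The strategy is to guess the letter with most places left. At each step the chance of being right is (largest number of places left) / (total places left). The expected number correct is the sum of these over the sequence, averaged over all possible sequences.

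- Totals of 10/10/10 fixed, no smaller blocks: 13.7 of 30 (46%).
- Blocks of 6, size known: 1/3 + 2/5 + 1/2 + 0.533 + 0.6 + 1 = 3.367 per block; × 5 = 16.8 of 30 (56%).
- Blocks of 3, size known: 1/3 + 1/2 + 1 = 1.833 per block; × 10 = 18.3 of 30 (61%).
- Unrestricted randomisation: 10 of 30 (33%), no gain.

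III.E does not say which applies. Unrestricted randomisation would yield exactly 10/10/10 with probability 30! / (10!³ × 3³⁰), about 2.7%, so the stated arm sizes suggest some restriction.

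**5. Check on the remedy.** If 45 kits (15 per arm) were put in one simple random order, the chance that the first 30 hold exactly 10 per arm is C(15,10)³ / C(45,30) = 3003³ / 344,867,425,584 = 0.079, about 8%. The list must therefore be balanced separately for the first 30 and the last 15.

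**The case against.** The strongest reply is that the main efficacy result has its own protection. III.B calls the BPRS the main outcome and has it rated from tape after the study; section IV bases the main efficacy test on the change from 0 to 2 weeks. The dopamimetic decision comes at the end of that period, so it cannot bias that test. This stands. A reader might infer that the primary efficacy test is compromised, but the documents do not support that. The protection is large rather than complete: the interview itself is held at the visit, and III.B does not say that the tape rater is kept away from the cards.

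Second, no emergency opening is planned. III.F.1 keeps the envelope sealed until 30 patients are enrolled, and III.D.2 passes the code sealed to the consultant and keeps investigators uninformed through any extension. This also stands. The point concerns what a break would reveal, not a prediction that one will occur; nor do the documents say that the study team itself reads the key at 30.

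Third, a reader might infer that selection bias is established. It is not. A guessed letter is not a guessed treatment until the letter is decoded, the block figures rest on a method that III.E does not state, and nothing says who dispenses cards or tracks letter counts.

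Fourth, it is tempting to assume that one clinician rates, titrates and enrols. The protocol does not assign these roles. Patients and caretakers see only one patient's cards and cannot pool, so for the CGI the pooling concern applies to the physician's rating.

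**Conclusion.** The concern holds as a defect of labelling and code-break design. By the wording of III.F.1 alone, opening the key for one patient unblinds all 30 (or 45), and decoding one letter unblinds 10 (or 15). III.G offers nothing further. The threat is mainly to the physician's CGI, the UPDRS motor ratings and the week-2 dopamimetic decision with the weeks 2-4 results that follow it.

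The size of the pooling effect depends on assumed side-effect rates: over the sets tried, the placebo letter is identified 67% to 98% of the time with 10 patients per letter. Predictability of the next letter is a lesser, conditional point: about 13.7 of 30 against 10 if exact totals are enforced, more with known small blocks, none under unrestricted randomisation. The scheme is worth changing before supplies are packed, because labels already in use cannot be made uninformative later.

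**What to change.** - Label each patient's set of weekly cards with a unique kit number and no arm letter.
- Have the supplier or pharmacy hold the random kit-to-arm list, balanced separately as 10 per arm in kits 001-030 and 5 per arm in kits 031-045, so that the look at 30 patients keeps its planned arm sizes.
- Replace the single key with one sealed code-break envelope per patient.
- Send the list directly from its holder to the statistical consultant at the 30-patient look.
- Amend III.E, III.F.1 and III.G to say this.

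A break would then expose one patient, and past labels would say nothing about the next assignment. Guessing about an individual patient from that patient's own side effects would remain possible; no labelling scheme removes it. The cost is slightly more packaging and labelling work, including 45 small envelopes, with no extra visits or staff.

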#### **G. Blinding**

The study will be conducted in a double-blind fashion. See III.F.1., immediately above.

#### **H. Concomitant Therapy**

Concomitant therapy of Parkinson’s disease including levodopa, carbidopa, selegiline, and dopamine agonists will be allowed if it satisfies the Inclusion and Exclusion Criteria given in section III.D.1. above. However, we will make every reasonable effort not to *change* the dose of any CNS-active medication during the 4 weeks of this study. The exception will be when we allow for upward titration of dopamimetics at the 2-week visit, if indicated.

